### **11.4. Additional studies**

It is the intention to repeat the Songheart study with an identical design in Israel with the purpose of subsequently being able to add data from the two studies together and thus increase the overall statistical power.

### **11.5 Analysis of substudies:**

Separate analyses will be performed with regard to:

The effect of intervention in the following subgroups:

- a. Age (<65, ≥65)
- b. Gender
- c. Heart failure (yes,no)
- d. Diabetes (yes,no)
- e. Time since last MI or invasive procedure: <2 yr, ≥2 yr.

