## 3) Several sub studies are planned:

1. Due to the chosen randomization procedure it will be possible to perform analyses on the randomized intervention trial on the subgroups listed in section 8: age, gender, diabetes mellitus, heart failure, time from last myocardial infarction or invasive cardiological procedure. Degree of depression is listed among the main purpose, section 2.
2. Comparison of the chosen PPS measure with another and established algometer.

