## 11. Statistics

### 11.1 Power and calculation of the size of the study population

The primary analysis is based on the depression score of the MDI questionnaire. The prevalence of depression measured as a MDI score  $\geq 20$  was found to be approximately 20 % in patients with ischemic heart disease (Olsen et al 2003; Bech P 2001). In a study with 292 office workers, the prevalence of a MDI score  $\geq 20$  was twice as high in people with a PPS measure  $\geq 60$  compared to people with PPS  $< 40$  (Ballegaard et al 2011). Against this background, it is estimated that among patients with ischemic heart disease who at the same time have an elevated PPS measure the prevalence of an MDI  $\geq 20$  is increased by 80 % compared to patients with ischemic heart disease as a whole, i.e. 36 %.

The Minimal Important Difference (MID) is set at 0.4 when the effect of active treatment is compared to control treatment. MID in terms of improvement of a MDI score is set at 5 points on the MDI scale when the active and control groups are compared. The standard deviation of improvement in both groups is set at 9 units on the MDI scale. Alfa is set at 5 %, Beta at 20 %. Against this background, 50 patients with an MDI score  $\geq 20$  are required in each group, thus 300 patients in total when safety margins of 10 % of the estimated values are included.

An interim analysis on the first 60 patients included showed, that the anticipated prevalences for MDI score were different than found. Therefore the cutpoint on the MDI scale was changed to MDI score = 15.

- Effect size is calculated from all included patients (on intention to treat basis)
- Effect size is a fraction that consists of the difference in a MDI score from before intervention till after treatment for the active group, minus the same

difference for the control group divided by the spread of the change in MDI score, when taking all patients together. In a review of all of the 12 SSRI preparations that the FDA has approved for treatment of depression, the average effect size is 0.3 (Turner et al., 2008). Example: the MDI score in active group changes from 24 to 11 ( $24-11 = 13$ ); while the MDI score for the control group changes from 24 to 14 ( $24-14 = 10$ ). This change in the MDI score is  $13-10 = 3$ ; if the spread (standard deviation) on the MDI score overall are 7.5, the effect size will be  $3/7.5 = 0,4$  ([name], 2010).

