## 11.2 Analysis of the effect variables

Five percent (5 %) will be used as significance level in all statistic tests.

The statistical analysis will look at two groups of cardiac patients separately: 1) those patients for whom all therapeutic approaches have been exhausted and 2) the rest. One joint analysis will be made if it is statistically reasonable. The statistics are compiled on an "intention to treat basis"; meaning that all enrolled patients are included in the subsequent analysis.

In the statistical analysis, subgroup analysis will be made for the patients with the highest PPS values: e.g. all patients with  $PPS \geq 75$ ; or for the highest quartile of PPS values.

"Closed test procedure" will be used to analyze data after 3 and 12 months in terms of the assessment of the treatment effect:

- First priority hypothesis: The Ull Care program improves the degree of depression measured by a MDI depression score, measured after 3 months of intervention.
- Second priority hypothesis: The Ull Care program improves health economic variables, measured after 12 months of intervention.
- Third priority hypothesis: The Ull Care program improves the frequency of clinical events, measured after 12 months of intervention.

Baseline measurements will be co-variant variables in relation to the applied stratification variable: the degree of depression measured by the MDI scale. Data from before and after the intervention will be analyzed separately. Delta values for

the active and control group respectively will be compared to analyze a possible treatment effect. All secondary and tertiary effect variables will be analyzed after the intervention through variance and regression analysis. If the premises for the proposed statistical analysis cannot be met, non-parametric analysis is used. Quality-of-life data will be analyzed to meet the directions of each of the questionnaires. All effect data will be presented a unifying table and primary, secondary and tertiary effect variables will be listed.

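### Sections 11.2 and 11.5 plan subgroup analyses without a treatment-by-factor comparison, so differing subgroup results are likely even when the effect is uniform

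*Protocol*

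**What the plan says.** Section 11.5 announces "Separate analyses will be performed with regard to" what it calls "The effect of intervention in the following subgroups". It lists age (under 65 or older), gender, heart failure, diabetes, and time since the last infarction or invasive procedure (under two years or longer). That makes five factors and ten levels.

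Section 11.2 states: "Five percent (5 %) will be used as significance level in all statistic tests". It adds that "subgroup analysis will be made for the patients with the highest PPS values", and offers two definitions as examples: PPS of 75 or more, or the top quartile. The closed test procedure in the same section orders three hypotheses (MDI at 3 months, health economics and clinical events at 12 months). No subgroup is among them.

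Section 3, item 3, ties the subgroups to the randomisation: "it will be possible to perform analyses on the randomized intervention trial on the subgroups listed in section 8". Its list includes time from last infarction or procedure. The minimisation factors in section 8 are age, gender, heart failure, diabetes and MDI score.

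The protocol states no interaction test, multiplicity adjustment or exploratory label for these analyses.

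**The concern.** A significant result in one level and a non-significant result in the other is not evidence that the effect differs. The smaller level simply has less power, and even equal halves will often fall on opposite sides of 5% by chance. Only a direct contrast of the two level-specific effects answers the question that a subgroup analysis asks.

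Followed as written, the plan invites statements that the programme works in women but not in men, or in patients without heart failure but not in those with it, when the effect is the same in all. If the programme has no effect, ten level tests at 5% offer several chances of an isolated positive result. The open high-PPS definition adds a cut that could be chosen after the results are known.

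**Working it through.** **Inputs.** Section 11.1 gives "Alfa is set at 5 %, Beta at 20"%, and "MID in terms of improvement of a MDI score is set at 5 points on the MDI scale", with an SD of improvement of 9. Section 12 requires a standardised effect of at least 0.4. Sections 7 and 11.1 give 300 patients, 150 per arm. Tests are taken as two-sided, which the protocol does not state. The protocol gives no subgroup prevalences, so all splits below are assumptions.

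**The plan's own figure.** n per group = 2 × [9 × (1.960 + 0.842)/5]² = 50.9, so 51 against the stated 50. With 36% prevalence, 100/0.36 = 278, and 278 × 1.10 = 306 against the stated 300. The sample size is reproduced closely and is not in question here.

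**Discordance for one factor, uniform effect d.** The power in a level with n patients per arm is approximately Φ(d/√(2/n) − 1.96). The two levels contain different patients, so P(one significant, the other not) = p₁(1 − p₂) + p₂(1 − p₁).

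- All 300 patients, d = 0.4: power 93%.
- 50/50 split, 75 per arm in each level, d = 0.4: p₁ = p₂ = 0.688, so discordance = 2 × 0.688 × 0.312 = 0.43.
- 80/20 split, 120 and 30 per arm, d = 0.4: 0.873 × 0.659 + 0.341 × 0.127 = 0.62.

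| Split (assumed) | d = 0.4 | d = 5/9 = 0.56 |
|---|---|---|
| 50/50 | 43% | 14% |
| 70/30 | 52% | 26% |
| 80/20 | 62% | 43% |
| 90/10 | 75% | 67% |

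**False positives with no effect.** If ten level tests were independent, the chance of at least one would be 1 − 0.95¹⁰ = 0.40. They are not independent, because the five factors re-divide the same patients. A simulation of 10,000 trials per scenario (150 per arm, normal outcome, five mutually independent binary factors) gives 28–29%. The high-PPS subgroup is not counted.

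**All five factors together.** In the same simulation with a uniform 0.4 SD effect, at least one factor is discordant in 76% of trials when all splits are 50/50. With assumed smaller-level shares of 50, 25, 20, 20 and 50% the figure is 92%.

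**The alternative.** One interaction test per factor at 5% gives 1 − 0.95⁵ = 0.226 over five tests (21–22% simulated), whether or not there is an overall effect. Its power to detect a between-level difference of 0.4 SD is Φ(0.4/SE − 1.96):

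- 50/50: SE = √(4/150 + 4/150) = 0.231, power 41%.
- 80/20: SE = √(4/240 + 4/60) = 0.289, power 28%.

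The difference detectable with 80% power is 2.80 × SE, which is 0.65 SD at 50/50 and 0.81 SD at 80/20.

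**The case against.** Section 11.5 is a list of factors. It names no test, model or significance level, and its separate analyses may only mean separate from the main analysis in section 11.2. The 5% comes from a general sentence elsewhere. Interaction terms, intervals and exploratory labels are often left to an SAP, which is not available here. This stands as far as wording goes: a reader might infer that the protocol literally prescribes a 5% test in each level and excludes interaction tests, and it does neither. Within-level testing is the natural reading, and on any reading the protocol plans subgroup effects without a between-level comparison.

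The size also depends on inputs. At the planning effect, discordance at an even split is 14%, not 43%, and every split is assumed. A reader might also take 40% as the false-positive rate, but that needs an independence that fails here.

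The remedy is imperfect. Five interaction tests at 5% cut the no-effect error only from about 29% to about 22%, and their power is low. Their gain is protection against spurious discordance.

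Finally, these are substudies. The success criteria and the closed test procedure do not use them.

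**Conclusion.** The point holds in a moderate form. The protocol plans subgroup effects and a 5% level for all tests, leaves the high-PPS cut open, and states no treatment-by-factor comparison. On the natural reading, discordant subgroup results are likely under a uniform effect: per factor, 43% at 50/50 and 62% at 80/20 for 0.4 SD, and 14% at 50/50 for 0.56 SD, rising with unequal splits. With no effect, at least one level test is falsely positive in about 29% of trials. These figures rest on two-sided tests, 300 analysed patients, assumed splits and, for the five-factor results, mutually independent factors.

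Two stronger conclusions are tempting but unsupported. The trial's main conclusion is not at risk, because section 12 does not depend on subgroups. Nor is the time-since-infarction subgroup invalid: a baseline factor need not be a minimisation factor to define a subgroup. Section 3 merely attributes it to section 8 wrongly, with no numerical consequence.

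**What to change.** - In section 11.5, for each of the five factors, fit one model on all randomised patients with arm, factor and arm-by-factor interaction. Report the interaction p-value and the level-specific estimates with confidence intervals, and label the results exploratory.
- State that five interaction tests at 5% still carry about 22–23% family-wise error unless adjusted. Testing each at 1% would bring it to 1 − 0.99⁵ = 4.9%. State also that power is low (about 41% for a 0.4 SD difference at 50/50, 28% at 80/20).
- In section 11.2, replace the open high-PPS choice with an arm-by-baseline-PPS interaction, or fix one cut before unblinding. A continuous term uses all patients but assumes a form, usually linear, which should be stated.
- In section 3, say that time since infarction or procedure is a baseline subgroup that is not among the minimisation factors.

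The change is to wording and analysis only and needs no further patients or data. The price is that fewer subgroup claims will be possible, and fewer still if the interaction tests are adjusted.

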## 12. Success criteria

The result of the study will be concluded as positive, if the following results are reached:

Compared to the control group, the active group obtains a significant improvement in MDI depression score and with a therapeutic effect size of at least 0,4 when the effect in the active group is compared to the control group (see point 11.1 for exact calculation of the effect size).

When compared to the control group, the active group obtains a significant improvement in mean PPS measurement measured by a professional instructor and with a MID of 10 units on the PPS scale.

The patient does not experience any increased risk in connection with the intervention measured as no increase in blood pressure or serum cholesterol after treatment, Both parts are measured as mean values for the two variables in the active group when the baseline values are compared at the end of the treatment period.

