#### *1.4.6 Pulse and Pressure-rate Product as stress markers*

Resting pulse has proven to have a prognostic value in ischemic heart disease (Lanza et al., 2006), and the link has proven to be the degree of persistent stress (Rogowski et al., 2007). Pressure-rate Product (PRP) is the product of the systolic blood pressure and the pulse, which is used in cardiology as an index of heart's ability to obtain oxygen and therefore reflects the work of the heart. The work of the heart is mainly controlled by beta-adrenergic catecholamine receptors (Opie, 2001), which makes the PRP suitable as an indicator of the sympathetic tonus in the heart (Noble, 2002) and suitable as a prognostic marker of ischemic heart disease (Villella et al., 1999).

A previous study has shown a significant link between resting pulse, PRP and the PPS measure (Ballegaard et al., 2009), yet we have opt to use blood pressure, pulse, Pressure-rate product and serum cholesterol as primary and secondary variables in the Songheart study because the study's primary target group are receiving medication that affects these variables.

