## 4. Design

Prospective, randomized, controlled, single-blinded study with 50 % allocation ratio for intervention. The time course of the intervention and control group is parallel. The study takes place at Herlev Hospital and is open to the following: participating patients and the instructor of the active group. The study is blinded to all others, including the statisticians who must make the main analysis. The personnel conducting the clinical examinations do not have access to the documents containing information about the treatment or treatment procedures. This is to prevent bias in the comparison between the treatment groups.

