## **7. Practical course (including flowchart)**

Using databases of cardiac rehabilitation patients from Gentofte and Herlev Hospital respectively approximately 600 patients with complete cardiac rehabilitation course > 6 months ago, to ensure a steady state in regard to the efficacy of the given cardiac rehabilitation, are identified. The patients are invited by letter to participate in the study.

It is expected that about 450 will accept. These are convened to an examination at Herlev Hospital Medical Department O.

All patients sign the consent form and go through the physiological preliminary examination.

Patients with PPS < 60 are ended immediately, and a subset of the first 50 patients with PPS < 45 are invited to a measuring of their body composition.

Since it is expected that 2/3 of patients have an elevated PPS measure ( $\geq 60$ ), 300 patients with PPS  $\geq 60$  are randomized to either an active or control group with 150 in each:

**Control group:** Continue their own efforts in extension of the already given cardiac rehabilitation and receive a textbook on general stress management (REHAB + CARE).

**Active group:** the same plus the Ull treatment program (REHAB + ULL).

All included patients will at baseline be offered an additional measurement of body composition.

Intervention period: 3 months.

Both the control and active group continue with the given medical treatment. If there is a change in heart condition including possible side effects of medication, the medication is adjusted according to the procedures in the rehabilitation programs at the hospital the patient is assigned to (Gentofte or Herlev Hospital). If possible, the medication should remain stable during the 3 months of the observation. The patient and the patient's own doctor are informed that the aim of the study is that any adjustment of cardiovascular medicine happen after contact with the project nurse (perhaps through a telephone hot-line).

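### The safety condition for a positive trial compares the active arm only with its own baseline and has no margin, so it tracks background change rather than the intervention

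*Protocol*

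**What the plan says.** Section 12 (Success criteria) opens: "The result of the study will be concluded as positive, if the following results are reached". Three results follow.

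- The first is a comparison between arms: "Compared to the control group, the active group obtains a significant improvement in MDI depression score", with a minimum effect size of 0.4.
- The second, on PPS, is also between arms, must also be significant, and carries a minimum difference of 10 units.
- The third concerns risk from the intervention. It requires "no increase in blood pressure or serum cholesterol after treatment" and defines the measurement so: "Both parts are measured as mean values for the two variables in the active group when the baseline values are compared at the end".

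The third result has no control comparison, significance requirement, margin or confidence limit. It speaks of two variables but does not say which blood pressure is meant.

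A concurrent comparator exists. Section 4 describes a "Prospective, randomized, controlled, single-blinded study with 50 % allocation ratio for intervention", and under Section 7 the patients "are randomized to either an active or control group with 150 in each". The flowchart in Section 7.1 schedules blood pressure and blood samples at 0 and 3 months, and Section 7 recalls both groups for the second visit.

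On background treatment, Section 5.2 requires cholesterol-lowering and antihypertensive medication. Section 1.4.6 refers to these measures with the words "because the study's primary target group are receiving medication that affects these variables". The rest of that sentence is garbled, but this clause is clear. Section 7 says that, if the heart condition changes, "the medication is adjusted according to the procedures in the rehabilitation programs".

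**The concern.** The condition is meant to show whether the intervention adds risk. A before-after change in one arm cannot show that, because it adds the effect of the intervention to everything else that moved over 3 months. The protocol itself names one such source, medication. Randomisation supplies the comparison that would separate the two, and this condition does not use it.

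The missing margin is a second, separate fault. An observed mean change is almost never exactly zero, so with no true change each mean is as likely to rise as to fall, whatever the sample size.

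Two wrong verdicts are possible. A trial with clear benefit on depression and PPS could be declared not positive because of chance or drift in two tertiary variables. A trial in which active patients did worse than controls could be declared free of added risk.

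**Working it through.** The protocol gives no pass or fail probability for this condition, so there is no stated figure to reproduce. The inputs from the document are the rule (Section 12) and 150 patients per arm (Section 7). The document gives no standard deviation for change in blood pressure or cholesterol. The ranges used below, 10 to 20 mmHg and 0.5 to 0.8 mmol/L, are assumptions.

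**1. No true change and no drift, any observed rise fails.** For two mean changes with correlation ρ:

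P(fail) = 1 − [1/4 + arcsin(ρ)/(2π)]

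- ρ = 0: 1 − 0.25 = 75%
- ρ = 0.3: 70%
- ρ = 0.5: 1 − (0.25 + 0.083) = 67%

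Neither the standard deviation nor the sample size enters. If systolic and diastolic both count (assumed correlation 0.5 to 0.7 with each other, 0.1 with cholesterol):

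P(fail) = 1 − [1/8 + (sum of the three arcsines)/(4π)] = 82% to 80%

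**2. Neutral intervention with drift.** With independent variables and SE = SD/√150:

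P(fail) = 1 − Φ(−d_BP/SE_BP) × Φ(−d_chol/SE_chol)

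| Drift (mmHg; mmol/L) | P(fail) over the assumed SDs |
|---|---|
| −2; −0.1 | 1% to 17% |
| −1; −0.05 | 21% to 43% |
| 0; 0 | 75% |
| +1; +0.05 | 94% to 99% |

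For example, −1 and −0.05 with SDs 10 and 0.5 give SEs 0.816 and 0.0408, so both z values are 1.22 and P(fail) = 1 − 0.890² = 21%.

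**3. Harm relative to control.** With SD 15, SE = 15/√150 = 1.22. The active-arm change is drift plus harm.

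- Drift −4, harm +3: change −1, and the blood pressure part passes with probability Φ(1/1.22) = 79%.
- Drift −6, harm +3: change −3, Φ(3/1.22) = 99%.
- Drift 0, harm +1: Φ(−1/1.22) = 21%.

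These are for blood pressure alone. In the first case the whole condition passes 0.79 × 0.5 = about 40% of the time if cholesterol is truly unchanged and independent, and up to about 79% if cholesterol clearly falls.

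**4. Alternative reading.** If the condition meant no statistically significant increase, a neutral intervention would fail 1 − 0.975² = 5% (one-sided 0.025 each) to 1 − 0.95² = 10% (one-sided 0.05 each) of the time.

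**5. Between-arm rule with a margin.** With 150 per arm, one-sided 0.025 and true difference zero:

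P(pass) = Φ(margin/(SD√(2/150)) − 1.96)

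| Variable | Margin | P(pass) |
|---|---|---|
| Blood pressure | 3 mmHg | 74%, 41%, 25% at SD 10, 15, 20 |
| Blood pressure | 5 mmHg | 99%, 82%, 58% at SD 10, 15, 20 |
| Cholesterol | 0.2 mmol/L | 93%, 58% at SD 0.5, 0.8 |
| Cholesterol | 0.3 mmol/L | above 99%, 90% at SD 0.5, 0.8 |

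The margins only illustrate the calculation. A between-arm rule without a margin would still fail a neutral intervention 75% of the time with independent variables, so both changes are needed.

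**The case against.** **The failure rate rests on assumptions.** It needs the point-estimate reading, zero within-arm change and variables that are not strongly correlated. This stands, and no single figure should be treated as a property of the rule. The literal reading is still the natural one, because significance is required in the first two conditions and not in this one. The 5% level that Section 11.2 sets for all tests could support the significance reading. The rule would then fail a neutral intervention far less often but would still ignore the control arm.

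**The protocol expects falls.** Section 1.6 reports reductions of 10% in blood pressure and 13% in cholesterol among office workers. If that carries over, the condition is easily met. This also stands, but a safety condition should work when the expectation is wrong.

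**Medication is partly controlled.** Section 7 asks for stable medication where possible and ties adjustment to a change in heart condition. Section 5.3 excludes recent changes in angina or heart-failure medication, and Section 6.3.5(d) records changes. These limits reduce drift but do not remove it.

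**Harm would not be invisible.** Both variables are tertiary outcomes, and Section 11.2 compares changes between arms. That is so. The fault lies in the success verdict, not in what is reported.

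A reader might go further on three points that the document does not support.

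- *A ceiling on the chance of a positive trial.* At a true effect size of 0.4, the MDI condition is met half the time, and 0.50 × 0.25 = 12.5%. At 5/9 = 0.56 the figures are 0.91 × 0.25 = 23%. These are not upper limits: a correlation of 0.3 between the two safety changes raises the 0.25 to 0.30, giving 15% and 27%, and downward drift raises them much further.
- *Regression to the mean as a main cause.* Patients are selected on PPS, not on blood pressure or cholesterol.
- *A firm gate on all 12-month work.* Section 7 ties those analyses to the success criteria. Section 6.3.4 words its gate as the primary and secondary objectives while pointing to Section 12, and the order in Section 11.2 places only MDI ahead of the 12-month hypotheses.

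**Conclusion.** The point holds. The third success condition attributes risk to the intervention from an uncontrolled change in one arm and has no tolerance for chance. Following it as written can give the wrong verdict in either direction.

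Under the literal reading and no drift, a neutral intervention fails about 67 to 75% of the time for correlations from 0.5 down to 0. The figure is about 80% if both pressures count. These figures do not depend on any assumed standard deviation. Drift of 1 to 2 mmHg with 0.05 to 0.1 mmol/L moves the rate from near 1% to near 99%, given the assumed standard deviations. That spread is the main evidence that the condition measures background change.

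A reader might infer that the rule both fails a harmless intervention three times in four and lets substantial harm through. These results belong to different circumstances: the first needs no drift, and substantial harm passes readily only with downward drift. The −4 mmHg drift is an assumption, and in that example the whole condition passes only about 40% of the time if cholesterol is unchanged.

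The primary MDI comparison, the randomisation and the data are unaffected.

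**What to change.** Replace the third condition in Section 12 with a between-arm one. Use the baseline-adjusted active minus control difference at 3 months in a named blood pressure measure and in serum cholesterol, and require the upper confidence limit to lie below a margin for each. The sponsor should justify the margins and fix them before unblinding. Beside it, report by arm the medication changes already recorded under Section 6.3.5(d).

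Before adopting it, check with realistic standard deviations that 150 per arm gives a harmless intervention an adequate chance of meeting both parts. If not, the sponsor must reconsider whether this should be a required success condition or a reported safety estimate.

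The cost is one amended paragraph and two agreed margins, with no new data. The real downside is power. A tight margin could fail a harmless intervention about as often as the present rule: 3 mmHg at an assumed SD of 15 passes 41% of the time, and with 0.2 mmol/L at SD 0.8 (58%) the joint chance is about 0.41 × 0.58 = 24% if independent. With 5 mmHg and 0.3 mmol/L at the same SDs it is about 0.82 × 0.90 = 74%.
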